# The Effect of Transcranial Alternating Current Stimulation With Cognitive Training on Executive Brain Function in Individuals With Dementia: Protocol for a Crossover Randomized Controlled Trial

**DOI:** 10.2196/37282

**Published:** 2022-04-27

**Keywords:** transcranial alternating current stimulation, Alzheimer disease, cognitive impairment, double blind, treatment, placebo-controlled, randomized, crossover, dementia, cognitive

## Abstract

**Background:**

Although memory and cognitive declines are associated with normal brain aging, they may also be precursors to dementia.

**Objective:**

We aim to offer a novel approach to prevent or slow the progress of neurodegenerative dementia, or plausibly, improve the cognitive functions of individuals with dementia.

**Methods:**

We will recruit and enroll 75 participants (older than 50 years old with either mild cognitive impairment or probable early or moderate dementia) for this double-blind randomized controlled study to estimate the efficacy of active transcranial alternating current stimulation with cognitive treatment (in comparison with sham transcranial alternating current stimulation). This will be a crossover study; a cycle consists of sham or active treatment for a period of 4 weeks (5 days per week, in two 30-minute sessions with a half-hour break in between), and participants are randomized into 2 groups, with stratification by age, sex, and cognitive level (measured with the Montreal Cognitive Assessment). Outcomes will be assessed before and after each treatment cycle. The primary outcomes are changes in Wechsler Memory Scale Older Adult Battery and Alzheimer Disease Assessment Scale scores. Secondary outcomes are changes in performance on tests of frontal lobe functioning (verbal fluency), neuropsychiatric symptoms (Neuropsychiatric Inventory Questionnaire), mood changes (Montgomery-Åsberg Depression Rating Scale), and short-term recall (visual 1-back task). Exploratory outcome measures will also be assessed: static and dynamic vestibular response using electrovestibulography, neuronal changes using functional near-infrared spectroscopy, and change in spatial orientation using virtual reality navigation.

**Results:**

As of February 10, 2022, the study is ongoing: 7 patients have been screened, and all were deemed eligible for and enrolled in the study; 4 participants have completed baseline assessments.

**Conclusions:**

We anticipate that transcranial alternating current stimulation will be a well-tolerated treatment, with no serious side effects and with considerable short- and long-term cognitive improvements.

**Trial Registration:**

Clinicaltrials.gov NCT05203523; https://clinicaltrials.gov/show/NCT05203523

**International Registered Report Identifier (IRRID):**

DERR1-10.2196/37282

## Introduction

### Background

Due to medical advancements and healthier lifestyles, lifespans are increasing. However, as longevity increases, cognitive abilities such as executive function, memory, reasoning, and processing speed deteriorate [1]. While deterioration may be part of normal aging [2], declines in cognitive function or associative and spatial memories can also be precursors to dementia [3]. There is currently no cure for dementia, however, there is hope that the onset of the disease can be delayed, or its progression slowed, by living a brain-healthy lifestyle. This hope is based on brain neuroplasticity, as well as individuals’ cognitive reserves [4]. It has been suggested that constructing a cognitive “reserve capacity” [5] can help seniors to maintain cognitive function, which was later supported by neuroimaging studies that showed increased contralateral hemispheric activity in right frontal regions for both working memory [6] and episodic memory [7] in aging populations.

Recently, many interventions and studies [8-10] have reportedly demonstrated cognitive improvement in older adults from cognitive training (brain exercises or brain games), if they are used frequently and regularly; however, cognitive improvements were largely observed in the same tasks, with minimal far-transfer effects being observed. A 2018 study with 72 participants (20 to 62 years) showed evidence against transferable gains from cognitive function training that consisted of spatial training and working memory tasks [11]. However, in almost all studies that have considered the effect of brain exercises on the cognitive function of adults and older adults, participants performed their exercises without a trainer [8,11]. Conversely, significant cognitive improvement in individuals with mild or moderate dementia has been demonstrated when they participated in daily brain exercises in a regimented, structured learning environment with the help of a tutor, and improvements transferred to their daily life beyond the practiced exercises as the outcome measures were independent of the practiced tasks [9,12-14].

The application of transcranial alternating current stimulation—an external oscillating electrical field that induces cortical activity—either in addition to or independent of brain exercises, on cognition has been explored. It is a relatively inexpensive, easy to administer, and safe tool for noninvasive brain stimulation. Transcranial alternating current stimulation has been demonstrated to both modulate and entrain the ongoing network oscillations in a frequency-specific manner [15], by using appropriate stimulation parameters (ie, frequency, intensity, duration, and anatomical location) to manipulate the phase, the rhythm, and the power of neural oscillations, through in vitro and in vivo experiments [16]. Because it operates in a frequency- and phase-specific manner, which offers the possibility to demonstrate causal relations between oscillations and behavior [17,18], interest in transcranial alternating current stimulation has significantly increased in the past decade. Furthermore, the therapeutic potential of transcranial alternating current stimulation has led many researchers to study its applicability as a treatment option for numerous neurological and psychological disorders [14,18,19]. However, there has been little investigation into the potential effect of transcranial alternating current stimulation on older adults with cognitive impairments associated with dementia. Moreover, much of the research on transcranial alternating current stimulation involves testing participants’ cognitive performance during or immediately after stimulation sessions.

In a recent pilot study [14], we demonstrated that the addition of transcranial alternating current stimulation to a cognitive training program improved participants’ working memory, and improvements remained for a longer period after the intervention; however, there were several shortcomings in this study. Aside from having a limited sample size, the main shortcoming was that placebo effect was not analyzed. We aim to address shortcomings by employing a better study design to investigate the efficacy of combined transcranial alternating current stimulation and cognitive training on the dementia population (Clinicaltrials.gov NCT05203523).

### Objective

We aim to investigate the effect of transcranial alternating current stimulation when paired with simultaneous cognitive training on the cognitive status of the dementia population as well as the predictability of participant responses to active transcranial alternating current stimulation at baseline.

### Hypotheses

We hypothesize that (1) better cognitive performance will be evident for patients’ active treatment periods compared with those from the sham periods; (2) in both groups, statistically significant improvement in cognitive performance will be evident immediately postintervention compared with baseline, and (3) a statistically significant difference in cognitive improvement will be found between the active and sham transcranial alternating current stimulation groups.

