## Methods

### Experimental Design

This is a randomized, crossover, double-blind, placebo-controlled study. Participants with cognitive impairments are recruited at 1 of 2 sites (Manitoba and Alberta) and randomized into 2 groups, with stratification by age, sex, and cognitive level (measured with Montreal Cognitive Assessment [20]) for randomization. Group 1 participants receive active transcranial alternating current stimulation simultaneously with cognitive exercises. Group 2 participants receive sham transcranial alternating current stimulation simultaneously with cognitive exercises. Participants who cannot tolerate the application of transcranial alternating current stimulation and focus on the cognitive exercises at the same time are enrolled in a third group, in which they only receive cognitive exercises but otherwise follow the same protocol as those in group 1 and group 2. The outcomes of group 3 will be analyzed separately. Standard cognitive assessments are performed before and after treatment, as well as at a scheduled follow-up visit 3 months postintervention. Both participants and assessors remain blind to the type of treatment (active versus placebo) until the end of the study.

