### Treatment Protocol

Training for all groups occurs in-person over the course of 4 weeks, 5 days per week (excluding weekends); there is an 8-week wash-out period prior to group crossover. On each day, participants attend two 30-minute training sessions using an app (MindTriggers) with a 30-minute break in between. Assessments occur at baseline (week 0), postintervention (weeks 5 and 11), at a follow-up (week 16), and at a long-term follow-up (week 27). Assessment at week 11 is considered to be baseline for the second cycle. No crossover occurs for participants assigned to group 3 (Figure 1).

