### Outcome Measures

At each assessment, 9 tests are conducted over 2 days due to time constraints. The first assessment day comprises the Wechsler Memory Scale Older Adult Battery [27], Montgomery-Åsberg Depression Rating Scale, a verbal fluency test for speech analysis, a visual 1-back task [28], virtual reality navigation [29], the Neuropsychiatric Inventory Questionnaire, and functional near-infrared spectroscopy. The second assessment day includes electrovestibulography and the Alzheimer Disease Assessment Scale (ADAS) cognitive subscale. An assessor is assigned to each participant and performs all 4 assessments with the assigned participant. Only the study participant and the research personnel designated to administer assessments are present during assessments.

The primary outcomes are the changes in patients’ scores from baseline in the Wechsler Memory Scale Older Adult Battery and ADAS cognitive subscale assessments. Alternate forms of the ADAS cognitive subscale word lists are employed at each visit to reduce possible practice effects. The secondary outcomes are change in 1-back, Neuropsychiatric Inventory Questionnaire, and Montgomery-Åsberg Depression Rating Scale performance. The 1-back test presents a sequence of random shapes and participants must recall whether a presented object is a repeat of the previous object [28]. Neuropsychiatric Inventory Questionnaire is used to assesses neuropsychiatric symptoms and caregiver burden. Finally, to establish the presence of confounding variables, namely mood disorders, Montgomery-Åsberg Depression Rating Scale is evaluated at each assessment. The secondary exploratory outcome measures use a series of physiological monitoring tools to examine physiological changes in study participants before and after the intervention: (1) virtual reality navigation test to assess spatial orientation [29], (2) electrovestibulography [30-32] to assess static and dynamic vestibular response, (3) functional near-infrared spectroscopy (OctaMonas) [33] to record prefrontal cortex brain activities, and (4) verbal fluency to evaluate acoustic and linguistic changes (Table 2). It should be noted that the exploratory assessments will only be conducted at the Manitoba site.

**Table 2 table2:** Study outcome measures.

Outcome measures		Assessments

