## Discussion

This study’s design addresses both the short- and long-term effects of transcranial alternating current stimulation in a large study sample, by making comparisons with a sham treatment. Due to the COVID-19 pandemic, recruitment and enrollment slowed as a result of lockdowns imposed by the universities and health authorities.

The major limitation of the protocol is the lack of distinction between transcranial alternating current stimulation effects and cognitive training. A pilot study [14] showed cognitive improvement in patients with and without active transcranial alternating current stimulation treatment due to the combined effect of personal cognitive training. Thus, the independent effects of active transcranial alternating current stimulation treatment in comparison to sham transcranial alternating current stimulation are not discernible using this protocol. However, given the older age of study participants and often rapid degradation of cognitive function in dementia patients, it is the conscious effort of the research team to support brain stimulation even during sham treatments despite its confounding effect on results.

The study has been progressing as expected. Participants have found transcranial alternating current stimulation treatment to be agreeable and have adhered to outset eligibility criteria. Minor side effects, including fatigue and dizziness, have been appropriately addressed and managed during treatment.

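### Hypothesis 2 tests an uncontrolled before-after gain in both randomized groups, so a significant result cannot be attributed to training or stimulation

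*Protocol article*

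**What the plan says.** The Hypotheses section of the protocol article lists three statements. The second is that "in both groups, statistically significant improvement in cognitive performance will be evident immediately postintervention compared with baseline". The third is that "a statistically significant difference in cognitive improvement will be found between the active and sham transcranial alternating current stimulation groups", and the first likewise sets active periods against sham periods. Under Analysis, hypotheses 1 and 2 are named together as the ones to be examined by rank-based and permutation tests.

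Experimental Design describes the groups. For the first, "Group 1 participants receive active transcranial alternating current stimulation simultaneously with cognitive exercises". For the second, "Group 2 participants receive sham transcranial alternating current stimulation simultaneously with cognitive exercises". Participants who cannot tolerate stimulation form a non-randomized third group, in which "they only receive cognitive exercises but otherwise follow the same protocol as those in group 1 and group 2". No group goes without training.

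The primary outcomes are changes from baseline on the Wechsler battery and the ADAS cognitive subscale. The article recognises retest learning as a threat: "Alternate forms of the ADAS cognitive subscale word lists are employed at each visit to reduce possible practice effects". The Discussion says that a pilot study "showed cognitive improvement in patients with and without active transcranial alternating current stimulation treatment due to the combined effect of personal cognitive training", and it names the failure to separate stimulation from training as the major limitation.

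**The concern.** Hypothesis 2 is worded as a prediction of statistical significance, stands between two treatment comparisons and receives its own tests. But it compares each group only with its own past. Randomization and the sham protect a comparison between conditions; they do nothing for a comparison with baseline.

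Between baseline and the first postintervention assessment a score can rise because training works, because the test has been taken before, because participants expect to improve, or because they see staff five days a week. It can also fall through progression of the disease. An untrained or retest-only group would show how much of the change happens anyway, and this design has none.

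At stake is what the trial may conclude. One of its three stated hypotheses could be met with no effect of stimulation or training, or missed despite a real effect that decline has masked.

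**Working it through.** **The plan's own sample size.** Inputs from Sample Size Estimation: difference 20, SD 38, power 80%, significance 5% (taken as two-sided). The normal formula gives 2 × (1.960 + 0.842)² × 38² / 20² = 56.7, so 57 per group. The two-sample t-test solution is 57.6, so 58, which is the stated figure. Halved for the crossover, this is 29 per sequence group. The calculation concerns the between-group difference only; nothing in it refers to hypothesis 2.

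**What enters each comparison.** Write the expected change over a period as follows:

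- active: S + T + C
- sham: T + C

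Here S is the added effect of active stimulation, T the effect of training, and C everything else (practice, expectation, contact, disease course), taken as equal under both conditions within a period. Active minus sham leaves S. Hypothesis 2 tests S + T + C in one group and T + C in the other. With S = T = 0 it tests C in both, and C need not be zero.

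**How often C alone would satisfy hypothesis 2.** Inputs:

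- n = 29 per group, from the plan.
- Practice gain g = 5 or 10 Wechsler points: assumed, as the documents give no figure.
- SD of change: assumed. The article does not settle whether 38 is the SD of a score or of a change. If of a change, it is 38. If of a score, the SD of change is 38 × √(2(1 − r)), with retest correlation r also assumed: 29.4 at r = 0.7 and 17.0 at r = 0.9.

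A one-sample t-test on the change from baseline stands in for the planned tests. The critical value is t(0.975; 28) = 2.048, so the smallest significant mean gain is 2.048 × SD / √29. The probability of a significant gain in one group is the upper tail of the noncentral t with noncentrality g√29 / SD. Hypothesis 2 needs both groups, which are independent, so that probability is squared.

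| SD of change | Smallest significant gain | g | Noncentrality | One group | Both groups |
|---|---|---|---|---|---|
| 38 | 14.5 | 10 | 1.417 | 0.277 | 0.08 |
| 29.4 | 11.2 | 10 | 1.830 | 0.423 | 0.18 |
| 17.0 | 6.5 | 10 | 3.169 | 0.864 | 0.75 |
| 38 | 14.5 | 5 | 0.709 | 0.101 | 0.01 |
| 29.4 | 11.2 | 5 | 0.915 | 0.141 | 0.02 |
| 17.0 | 6.5 | 5 | 1.584 | 0.334 | 0.11 |

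**The randomized contrast under the same conditions.** In 40,000 simulated trials per setting (29 per group, no treatment effect, SD of change 20 or 38, common gain 0 to 20 points), a two-sample comparison of active with sham was significant in 4.7% to 5.0% of trials. A common gain leaves its error rate intact.

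**The case against.** The protocol predicts that improvement will be seen; it does not say that the improvement is caused by treatment. It nowhere calls hypothesis 2 confirmatory, and it sizes the trial on the between-group difference. A reader might infer that the authors claim a before-after gain as proof of efficacy. The text does not go that far. The sentence crediting training concerns the pilot, whose controls cannot be seen here. It shows how such a gain may come to be read, not how this trial will be reported.

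A reader might also infer that the Wechsler battery is repeated in identical form, because alternate forms are mentioned only for the ADAS word lists. The article does not say so, and a condensed article may leave test versions to the full protocol. That silence is no part of this point. Alternate Wechsler forms would not remove the problem in any case, since they supply no untrained comparator.

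On size, chances for a single group, or for all 58 participants pooled, are higher than those for both groups, but they do not describe hypothesis 2, which requires both. The both-group chances can be as low as 1%. Since decline acts against practice, even the direction of the net bias is unknown.

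Finally, the Discussion already concedes that stimulation and training are not separated. That concession does not mention retest practice, expectation or disease course, and it places no limit on hypothesis 2. What stands of the objection is that the article makes no explicit causal claim and that the size is uncertain. The lack of any comparator for a formally tested hypothesis is not answered.

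**Conclusion.** The point holds as a flaw confined to hypothesis 2. A significant before-after gain in both groups would not show that training or stimulation works, and its absence would not show that they fail. This follows from the design and needs no assumed figure.

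The chance of meeting the hypothesis through practice alone is illustrative: about 8% to 75% for a 10-point gain and about 1% to 11% for a 5-point gain, over an SD of change from 38 down to 17.0. It rests on an assumed practice gain, an assumed SD of change and a t-test in place of the planned tests. Hypotheses 1 and 3, the sample size and the randomization are untouched, provided such gains are alike under active and sham. It should be corrected, but it does not threaten the main comparison.

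**What to change.** - In Hypotheses and Analysis, remove hypothesis 2 from the hypotheses tested for efficacy.
- Report within-group change from baseline with confidence intervals, labelled descriptive. State that it combines any effect of training and stimulation with retest practice, expectation, staff contact and disease course.
- State that conclusions on efficacy rest only on active versus sham, and that the trial draws no conclusion on the effect of training.

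This changes wording only and adds no visits or participants. The cost is that the within-group significance claim is given up.

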## Methods

### Experimental Design

This is a randomized, crossover, double-blind, placebo-controlled study. Participants with cognitive impairments are recruited at 1 of 2 sites (Manitoba and Alberta) and randomized into 2 groups, with stratification by age, sex, and cognitive level (measured with Montreal Cognitive Assessment [20]) for randomization. Group 1 participants receive active transcranial alternating current stimulation simultaneously with cognitive exercises. Group 2 participants receive sham transcranial alternating current stimulation simultaneously with cognitive exercises. Participants who cannot tolerate the application of transcranial alternating current stimulation and focus on the cognitive exercises at the same time are enrolled in a third group, in which they only receive cognitive exercises but otherwise follow the same protocol as those in group 1 and group 2. The outcomes of group 3 will be analyzed separately. Standard cognitive assessments are performed before and after treatment, as well as at a scheduled follow-up visit 3 months postintervention. Both participants and assessors remain blind to the type of treatment (active versus placebo) until the end of the study.

### Recruitment

Approximately 75 patients with either mild cognitive impairment or probable early or moderate dementia, excluding Parkinsonian dementia, as confirmed by their treating physician will be recruited and tested over the course of this study. Participants are recruited from volunteers or doctor referrals.

Participant eligibility is confirmed in-person using the Montreal Cognitive Assessment, to assess the severity of dementia, and the Montgomery-Åsberg Depression Rating Scale, to assess for comorbid depression. Inclusion criteria are (all must be met): age between 50 and 95 years old; Montreal Cognitive Assessment score between 5 and 24; and the ability to read, write, and speak English fluently.

The exclusion criteria are diagnosis of Parkinson, Parkinsonian dementia, Huntington disease, speech-significant aphasia, intellectual disability, major depression or anxiety, bipolar disorder, schizophrenia, or any other major mood disorder; a history of epileptic seizures or epilepsy; inability to adequately communicate in English; vision or hearing that is sufficiently impaired to affect performance in cognitive tests; current substance abuse disorder; current participation in another therapeutic study for dementia; or a plan to change medication during the study period.

After the initial screening process and before randomization (Proc Plan, version 9.4; SAS Institute), participant tolerance to transcranial alternating current stimulation is tested with a 1-minute application as they focus on a cognitive exercise. If the participant cannot tolerate the application of transcranial alternating current stimulation, they are offered a chance to participate in the study as part of group 3. If they can tolerate the transcranial alternating current stimulation, they are randomized into either group 1 or group 2.

Prior to study participation, all patients and their primary caregivers are required to sign an informed consent form approved by the ethics board of each site of the study.

